## Abstract

This proof of concept study harnesses novel transdisciplinary insights to contrast two school-based smoking prevention interventions among adolescents in the UK and Colombia. We compare schools in these locations because smoking rates and norms are different, in order to better understand social norms based mechanisms of action related to smoking. We aim to: (1) improve the measurement of social norms for smoking behaviors in adolescents and reveal how they spread in schools; (2) to better characterize the mechanisms of action of smoking prevention interventions in schools, learning lessons for future intervention research. The *A Stop Smoking in Schools Trial* (ASSIST) intervention harnesses peer influence, while the Dead Cool intervention uses classroom pedagogy. Both interventions were originally developed in the UK but culturally adapted for a Colombian setting. In a before and after design, we will obtain psychosocial, friendship, and behavioral data (e.g., attitudes and intentions toward smoking and vaping) from ~300 students in three schools for each intervention in the UK and the same number in Colombia (i.e., ~1,200 participants in total). Pre-intervention, participants take part in a Rule Following task, and in Coordination Games that allow us to assess their judgments about the social appropriateness of a range of smoking-related and unrelated behaviors, and elicit individual sensitivity to social norms. After the interventions, these behavioral economic experiments are repeated, so we can assess how social norms related to smoking have changed, how sensitivity to classroom and school year group norms have changed and how individual changes are related to changes among friends. This Game Theoretic approach allows us to estimate proxies for norms and norm sensitivity parameters and to test for the influence of individual student attributes and their social networks within a Markov Chain Monte Carlo modeling framework. We identify hypothesized mechanisms by triangulating results with qualitative data from participants. The MECHANISMS study is innovative in the interplay of Game Theory and longitudinal social network analytical approaches, and in its transdisciplinary research approach. This study will help us to better understand the mechanisms of smoking prevention interventions in high and middle income settings.

## Introduction

### Adolescent Smoking Behavior

Globally, tobacco smoking constitutes the single most important preventable risk factor for chronic disease in high, middle and low income countries. While rates of smoking have declined in high income countries, they continue to rise or remain high in some low and middle income countries (LMICs) (1). The tobacco industry has recently focused more attention on LMICs, as its markets are eroded elsewhere. Smokers usually start as adolescents when the influence of social norms on behavior is most apparent. In schools in Bogotá, the current prevalence is the highest in the country, at 13.1% (2). Comparing the UK to Colombia, tobacco use prevalence among boys and girls aged 13–15 years old in Colombia is up to 6% points higher than in the UK (i.e., in Colombia 12% in boys and 9% in girls; in UK, 6% in boys and 8% in girls). The channels of influence on smoking behaviors can be direct and indirect, but peers consistently have a strong impact on behavior (3). As such, tobacco control interventions should target the age groups most susceptible to becoming lifelong smokers using the most effective channels.

Schools provide one setting for such interventions, particularly those aimed at shaping peer norms and interactions. In a recent systematic review of school-based smoking prevention interventions, only those with social competence and or social influence components were effective (4). However, most of the studies in that review were from high income settings. In another review of interventions evaluated in randomized controlled trials (RCTs) in LMIC settings, only three school based intervention trials invoked theories of social competence or social influence, and the authors concluded that any adaptation of evidence from high income settings must rest on a careful analysis of contextual factors to achieve similar results elsewhere (5). Even though *peer influence* is often a component of effective smoking prevention interventions (such as the *A Stop Smoking in Schools Trial* (ASSIST) intervention) (6), when Steglich et al. *modeled* peer influence in a subset of ASSIST schools (*n* = 3) using actor-based social network models, they acknowledged the need for future research to explore *how* peer influence varied across individuals and across schools (7).

### Social Networks and Social Norms

In order to develop better public health interventions, it is important to understand the mechanisms by which they exert their effects. Interventions that act on groups of people or whole populations may be more effective at reducing health inequalities than those that target individuals (8). Changing social norms is one way of affecting behavior in groups of people, but these social norms often depend on connections and shared “understandings” between members of the population. The connections between people are what characterize their shared “social network,” and this may affect the way that social norms spread among people. Public health scientists know surprisingly little about how best to measure and evaluate the spread of social norms and their effects on behavior.

The past decade has seen improved methodological rigor and a deeper understanding of both the theories and techniques of behavior change (9). There are clearly certain categories of population-level interventions whose effects are realized, at least in part, through changing social norms. Social norms themselves may depend on context or be conditioned and shaped by social networks. Thus, they span different levels of what is more broadly referred to as the “socio-ecological model” of behavior change (10). There has been a parallel and growing interest in understanding the effects of social networks on health related behavior (11–13).

Two competing theories have been offered about how health-related attitudes and behavior evolve and are transmitted across social networks, namely: (i) *selection* (homophily)—the tendency for people to establish relations with those they perceive to be most like (similar to) themselves; and (ii) by *influence*, whereby one adopts the behaviors that are seen as normative within the peer environment. Most observational studies show that both processes operate to varying degrees. Valente and Pitts (14) have recently articulated social networks' influence on behavior in terms of “the pressure individuals feel to conform to behavior when others in equivalent positions do so” and offers two putative mechanisms: (i) one via threshold effects whereby, for example, “low threshold” individuals adopt a new behavior before many of their peers have done so; (ii) and a second that weights “exposure” (and influence) according to structural characteristics of the network. While social networks are increasingly being exploited in the design and implementation of public health interventions (8, 15), a growing number of studies are now also testing interventions based on changing social norms related to health behaviors (16).

Within public health science, there have been few empirical studies exploring the *mechanisms* underlying the influence of social norms on health related attitudes and behavior. *Game Theory* is a branch of economics that has developed a canon of well-defined mathematical models for describing and understanding cooperation and competition amongst individuals and groups. However, while Game Theorists have increasingly adopted experimental approaches to test their more sophisticated models of social norms effects (17), the resulting insights have not crossed the disciplinary divide into the public health sciences. Previous attempts at identifying individual sensitivity to the effects of social norms have relied on actor-based *models* and have not actually attempted to empirically measure the effects directly. An experimental design rooted in Game Theory offers new ways to do this, and provides the opportunity to explore the behavioral economic mechanisms underlying the influence of social norms on health related attitudes and behavior.

### The Role of Game Theory Experiments in Studying Social Norms and Peer Influence

Kimbrough et al. (18) show that one can use simple rule following games to identify individual sensitivity to social norms. This norm sensitivity is a good explanation for cooperation, reciprocity and prosocial behavior in *Trust, Public Goods, Dictator*, and *Ultimatum* Games. Krupka et al. (20) use norm elicitation experiments to show that informal agreements affect behavior through a direct effect on the social norm and through an indirect effect by which the social norm appears to influence beliefs. These findings are significant because they identify a channel for behavior change that operates through a change in norms and beliefs at the individual level. This channel is a social channel: the norm is contingent on the peers who establish, transmit, and enforce the norm. However, previous work has not yet tested this channel where it can be most effective—nested within the social network of the individual. This study will test this channel within a social network. We will identify the impact of an intervention designed to change norms and beliefs. We will focus on smoking prevention in adolescents because it is an important public health concern and a critical population to reach.

The key objectives of this study are to:

develop and test new measures of social norms around smoking behaviors in adolescents using Game Theory approaches;better understand the diffusion of social norms in school settings in the UK, and in Colombia;better characterize the potential mechanisms of action of smoking prevention interventions in schools;learn lessons for the design and evaluation of behavior change interventions that invoke mechanisms that change social norms.

Our main research questions include:

How are individual psychosocial and cognitive traits at baseline related to individual sensitivity to social norms? (**H**_**0**_^**1**^: that they are independent);How does individual sensitivity to social norms cluster among friendship cliques and across school year groups? (**H**_**0**_^**2**^: that the individual social norms sensitivities among friendship cliques are un-correlated);How are average social norms, measured at the classroom and year group level, affected by social network structures? (**H**_**0**_^**3**^: that social norms and social network structures are independent);After each intervention: how are changes in attitudes, intentions and behaviors toward smoking related to social norms sensitivity at the individual level, and to average social norms at the class and year group level? (**H**_**0**_^**4**^: that the changes in smoking related attitudes, intentions, and behaviors are independent of norm-sensitivity at the individual level and the same in schools which offered each intervention);After each intervention: have smoking-related social norms changed and how are these changes correlated among friendship cliques? (**H**_**0**_^**5**^: that any changes in social norms are independent among members of the same friendship clique; we assume that there will be little change in measures of homophily across one semester).

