##### Measuring injunctive and descriptive norms

Injunctive norms reflect shared beliefs about what actions people *ought to* take; descriptive norms reflect shared beliefs about the prevalence of the norm (rather than beliefs about the behaviors that ought to be influenced by the norm). To measure injunctive and descriptive norms, we followed a protocol developed by Krupka and Weber (17). In a series of Coordination games, participants rated the social appropriateness of various actions that others might take and, in addition, they estimated the frequency with which people actually engage in certain behaviors. These games provide respondents with incentives to *match* their ratings/estimates to the responses of other participants in their year group in the session rather than to provide their personal opinions. In summary, we are measuring first-order beliefs about the prevalence of a norm against smoking/vaping and second-order beliefs about the social appropriateness of various smoking/vaping related behaviors.

The protocol measures injunctive norms because it creates an incentive to anticipate the extent to which others will rate an action as socially appropriate or inappropriate, and to respond accordingly. That is, if there is a social norm that some actions are more or less socially appropriate, respondents attempting to match others' appropriateness ratings are likely to rely on this shared perception to help them do so. Thus, the protocol elicits collective perceptions of appropriateness—our empirical measure of an injunctive social norm. This protocol was adapted to measure injunctive norms of prosocial behavior, injunctive norms about smoking behavior, and descriptive norms about smoking behavior. To encourage participants to *match* their ratings/estimates to the responses of other participants in their year group, they were paid £10.00 in Northern Ireland and £3.43 in Colombia for one “part” in the experiment only if their response was the same as the most common response given by other participants for a randomly selected question in that part of the experiment. For each “part” of the experiment, participants were told that at the end of the intervention, a coin would be flipped to determine whether they received their earnings from the baseline experiment or the experiment conducted after the intervention.

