##### Defining and identifying social norms unrelated to smoking

We first elicited pro-sociality norms unrelated to smoking behavior (as one type of negative control). We used a vignette describing a hypothetical Dictator game scenario as per Krupka and Weber (17) and Kimbrough et al. (18). The Dictator game is commonly used as a measure of social preferences, in particular, altruism (48). Such norms are unlikely to be affected by interventions targeted at altering smoking behavior. Hence, we measured norms of altruism before and after the intervention, as a “negative control.” We do not expect altruism norms to change after the smoking prevention interventions. In our norm elicitation experiment participants read a vignette that describes the choices an “Individual A” would be faced with, within the Dictator Game. “Individual A and Individual B from the class are randomly paired with each other. Individual A received £10.00 in Northern Ireland and £2.30 in Colombia. Individual A will then have the opportunity to give any amount of his or her money to Individual B. For instance, Individual A may decide to give £0.00 to Individual B and keep £10.00 for him or herself. Or Individual A may decide to give £10.00 to Individual B and keep £0.00 for him or herself. Individual A may also choose to give any other amount between £0.00 and £10.00 to Individual B. This choice will determine how much money each will receive, privately and in cash, at the end of the experiment.” We used a Coordination Game, as described above, to elicit the social appropriateness of each action available to “Individual A,” measuring injunctive norms of pro-sociality before and after the intervention.

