### Statistical Methods

#### Elicitation of Social Norms and Social Network Analyses

Injunctive social norms will be modeled quantitatively, such that a decision maker's “pay-off” u(a_k_) from a set of actions V {π(a_k_)} is related to the parameter γ ≥ 0, representing the degree to which the individual cares about adhering to social norms, in: u(a_k_) = V {π(a_k_)} + γN(a_k_), with the function N capturing the social norm, [i.e., the social appropriateness of action a_k_ denoted by N(a_k_)]. We let N_g_(a_k_) denote the social norms for group *g*, estimated from the Coordination games. γ is the key parameter reflecting individual sensitivity to the norm, estimated using the total number of balls allocated to the blue “rule following” bucket in the RF task. The Dictator and Coordination games allow us to identify norms related to prosocial behavior and to smoking related activities in the target population. We can then explore whether the norms related to smoking actually do change and whether data from the RF experiments help us predict who is more sensitive to following those changed norms after the intervention. We will also measure correlations (Spearman's rank correlation) between an individual's norms-sensitivity parameter and his/her decisions in the Donation game. We will use tobit regressions that allow for censoring, regressing the distance (Δ_SNdist_) between an individual's choice and the observed average norm (average Dictator choice) in the relevant reference group on his/her norm-sensitivity parameter. The tobit regression allows us to see if there is a statistically significant relationship between norm-sensitivity and the changed norms after the intervention. We will use similar techniques when examining social norms related to tobacco use and individuals' abilities to identify them in the Coordination game. For each behavioral vignette (whose appropriateness is rated), we will calculate a correlation between individuals' norms-sensitivity parameters, and their chosen score on the social appropriateness scale, after calculating (Δ_SNdist_). Scores on the appropriateness scale are categorical, requiring ordered probit regressions. We will conduct the above analysis both pre- and post-intervention but since we will have two observations for each individual, we will use the respective panel random effects versions (including a dummy variable to identify post-intervention observations). In all regressions, we will calculate standard errors clustered on school classes. We will account for individual participants' demographic and psychosocial characteristics, and dummy variables signifying intervention type (ASSIST or Dead Cool intervention) and country (Colombia or Northern Ireland).

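### H5 cannot separate spread of smoking norms among friends from friends sharing guesses in a paid matching game, and the altruism control is not put through the same friend-slope model

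*Protocol article*

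**What the plan says.** One stated objective is to "better understand the diffusion of social norms in school settings in the UK, and in Colombia" (Introduction, The Role of Game Theory Experiments in Studying Social Norms and Peer Influence). The same section sets the H5 question, "have smoking-related social norms changed and how are these changes correlated among friendship cliques", and its null hypothesis, "that any changes in social norms are independent among members of the same friendship clique". Under Statistical Methods, the H5 entry only refers back to Sample Size. That section speaks of network clustering of smoking-related norms and of no other norm.

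The norms are measured by game: Statistical Methods lets a function "denote the social norms for group *g*, estimated from the Coordination games". According to Measuring injunctive and descriptive norms, the games give "incentives to *match* their ratings/estimates to the responses of other participants in their year group in the session rather than to provide their personal opinions". The payment is £10.00 in Northern Ireland and £3.43 in Colombia, "only if their response was the same as the most common response given by other participants" on a randomly selected question. Pupils were also told that "a coin would be flipped to determine whether they received their earnings from the baseline experiment or the experiment conducted after the intervention".

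The altruism norm is elicited from Dictator vignettes with the same kind of game, before and after, and is called a negative control (Defining and identifying social norms unrelated to smoking). Its stated role concerns level: "We do not expect altruism norms to change after the smoking prevention interventions".

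**The concern.** A correlation of changes among friends is informative about spread only if shared game-play does not produce it too. Here pupils are paid for predicting a common answer, they know another round is coming, and they spend 8 weeks (Dead Cool) or 10 weeks (ASSIST) of intervention in the same year group. Friends who compare notes on the paid answer can move together without any change in what they believe about smoking.

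This runs along friendship ties, which is where H5 looks. The planned standard errors clustered on class, and the dummies for post-intervention, intervention and country, act at other levels. The instrumental-variable sensitivity analysis deals with unstable homophily. The one caution about repeat play, in the section on descriptive norms, concerns pupils learning what adults want to hear. At stake is how a positive H5 result may be worded.

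**Working it through.** **1. The plan's own figure.** Sample Size gives n = 300, standardised slope 0.16, 5% level, power over 80%. Sidedness is not stated; I take two-sided. By Fisher's z: atanh(0.16) × √297 = 0.1614 × 17.23 = 2.78; 2.78 − 1.96 = 0.82; power = Φ(0.82) = 79.4%. Other standard formulas give 78.9% to 80.2%, so the figure reproduces to rounding.

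**2. How much clustering of change gives a slope of 0.16.** Let ρ be the correlation of change between two friends and m the number of friends averaged. The standardised slope is ρ√m / √(1 + (m − 1)ρ). For groups of 5 (m = 4), ρ = 0.090 gives 0.090 × 2 / √1.27 = 0.16. For groups of 3 to 8 the required ρ runs from 0.12 down to 0.07.

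**3. Answer-sharing with no spread of norms.** Assumptions, none from the documents: 300 pupils, separate groups of 5, independent baseline answers, and a share q of groups giving one common answer at follow-up.

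*(a) Each agreeing group settles on its own answer, answers N(0,1).* Change has variance 2 and agreeing friends share a covariance of 1, so ρ = q/2.

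| q | ρ | Slope by formula | Simulated mean slope |
|---|---|---|---|
| 0 | 0 | 0 | −0.01 |
| 0.10 | 0.050 | 0.10/√1.150 = 0.09 | 0.08 |
| 0.15 | 0.075 | 0.15/√1.225 = 0.14 | 0.12 |
| 0.20 | 0.100 | 0.20/√1.300 = 0.18 | 0.16 |

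The simulated values sit slightly low because a leave-one-out slope has a small negative bias. Groups of 3 give about 0.06, 0.09 and 0.13 at the three non-zero shares. At q = 0.20 in groups of 5, H5 is rejected in 50% to 69% of runs, depending on the answer model and on how the critical value is set.

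*(b) Agreeing groups adopt the year-group mode, answers N(0,1).* The common answer is 0 in every agreeing group. The slope at q = 0.20 is about −0.01 to −0.02, as with no agreement, and rejection is about 5% to 6%.

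*(c) Agreeing groups adopt the mode of skewed six-point ratings.* With eight items and category probabilities 0.30, 0.25, 0.18, 0.12, 0.09 and 0.06, the slope in groups of 5 is 0.41 at q = 0.10 and 0.57 at q = 0.20. In groups of 3 it is 0.36 and 0.52. Other skewed settings gave 0.3 to 0.5.

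**4. What the control shows.** In (a) the average change is zero, so a check that the altruism level is stable can pass while the friend slope is inflated. In a six-point version of (a) at q = 0.20, with agreement on both parts, the smoking slope is 0.17 and the altruism slope 0.17. With clustering confined to smoking items they are 0.15 and −0.01. Fitting the control can therefore separate sharing across the whole game from clustering specific to smoking.

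**5. Precision of the difference.** When agreement is equally common in both parts, the difference has mean 0 and an SD of about 0.12 to 0.13 in model (a). A 95% interval is then roughly ±1.96 × 0.125 = ±0.25, wider than the 0.16 of interest. If two independent, equally precise slopes each had 80% power, the difference would have Φ(2.80/√2 − 1.96) = Φ(0.02) = 51%.

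**The case against.** Agreement among friends is conjecture. Payment is for the mode of a year group of about 80 to 100 pupils, not for matching friends, and nothing shows that pupils discussed the game. They knew of a second experiment, but the article does not say they were told the same items would return. This stands as a limit: the point is what H5 can distinguish, not what happened.

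The size depends on the model. This also stands. A reader might infer that answer-sharing would by itself yield the planned 0.16, but that holds only under step 3(a) with an assumed share of one group in five. Moreover, Sample Size words the 0.16 slope as norms sensitivity, which Statistical Methods estimates from the Rule-Following task, where nothing is paid for matching. The H5 question and other wording in Sample Size point to elicited norms, so the game-based reading is supported but the outcome is inconsistently worded.

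A reader might also infer that this slope is the study's main evidence of diffusion. The documents do not say so. The power calculation is an exemplar in a proof-of-concept study, and the donation task, questionnaire norm scales and focus groups allow triangulation. H3 also looks at clustering among friends before and after. None of these is tied to H5 as a control for game-play.

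Part of the supposed artefact is the construct itself: the game measures shared perceptions, and friends converging on what the year group finds appropriate is partly what the study seeks. Only strategic sharing of answers is spurious. Finally, which models a control enters is often left to an analysis plan. Here, though, the article states both the H5 target and the purpose of the control, and the ambiguity comes from the incentive and the repeat that it fixes.

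**Conclusion.** The concern holds in a limited form. As described, a positive H5 friend slope may reflect spread of smoking norms, friends sharing guesses about the paid answer, or both. The stated adjustments do not separate these, and the declared negative control is assigned only a check on level. No figure in the article changes. The possible distortion ranges from about zero to well above 0.16 according to the answer model and the unknown share of groups agreeing, so no single estimate of bias is warranted. A reader might go further and conclude that pupils colluded or that H5 is uninformative; the documents support neither.

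**What to change.** Fit the identical H5 friend-slope model to changes in the Dictator-vignette ratings and report that slope next to the smoking slope. As a supporting analysis, give the difference with an interval from permuting or resampling the network jointly for both outcomes. If the altruism slope is clearly above zero, do not attribute the smoking slope to norm diffusion alone.

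State two limits with the result. The control misses answer-sharing confined to smoking items, which is plausible because smoking is the topic of the interventions. Real spread of altruism norms would also raise the control slope. For these reasons, and because the difference is imprecise, it should not be a strict pass/fail rule for claiming spread.

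The cost is one further fit, plus the joint interval, on data already collected.
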